### Statistical analyses

2.8

The intention-to-treat principle will be used in the final analyses. Statistical analyses will be carried out using SPSS version 23.0 for Windows (Armonk, NY: IBM Corp.). The associations between any 2 groups of continuous variables will be tested using the independent sample or paired *t* test (normal distribution) or the Mann-Whitney *U* test (skewed data) and that of 2 groups of categorical variables with chi-square or Fishers exact test where appropriate. A series of multivariable analyses using binary logistic regression model will also be carried out to identify and control for several possible confounders of the primary and secondary outcome variables. Statistical significance will be defined as *P* < .05.

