### Standard prenatal care

2.4

All the women will receive their routine prenatal care which includes daily doses of ferrous gluconate (300 mg, equivalent to 60 mg of elemental iron) and folic acid (5 mg), and 4-weekly doses of malarial chemoprophylaxis in the form of Sulfadoxine-Pyrimethamine (SP) tablets (from enrolment to 36 weeks of gestation) or instead daily doses of Cotrimoxazole 980 mg for women with CD4 + cell counts < 200 cells/mm^3^ according to established protocol for *Pneumocystis carinii* prophylaxis^[20]^ irrespective of treatment assignments. Alternatively, daily proguanil tablet (100 mg) is given to women with known or recent allergy to Sulphonamides from enrolment to delivery. All women will also be commenced on ART at some point during their follow-up according to the National HIV prevention and treatment guidelines.^[21]^

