#### Data collection and management

2.5.1

At enrolment, the investigators will collect data on the participants’ socioeconomic status, education, and obstetric history, duration of HIV diagnosis (in months), WHO clinical stage of the disease,^[22]^ type and duration of ART use (in months), baseline Haemoglobin (Hb) levels (in g/dL), CD4 + cells count (in cells/mm^3^) and viral load (in copies/mL), and BMI (actual maternal weight is calculated by subtracting the estimated fetal weight at enrolment using a normogram chart from the measured maternal weight) (in kg/m^2^) using a structured interviewer-administered questionnaire. Gestational age is based on the date of the participant's last menstrual period, which will be obtained at the time of random assignment. Data collection begins on the day a participant is allocated into an intervention arm and continues until the termination of the trial or until the participant withdraws from the trial at any time for any reason. At delivery, data will be collected from the participants’ case notes on the latest CD4 + cells count and viral load (done within the last 6 weeks of delivery), WHO stage of the disease, and latest Hb levels. The total duration of supplement intake – selenium or placebo (in weeks), level of compliance to use of the supplement (good compliance level is defined as usage of at least 10 of the 16, 2-weekly prescribed tablets), mode of delivery, gestational age at delivery (in weeks) and the baby's birth weight (in grams) will also be recorded in the questionnaire. Original data will be transferred to an electronic database system located in a guarded facility at the trial site by the research assistant. Access to the study data is restricted. The PI will have the access to the final dataset. An independent steering committee will monitor and examine strict compliance with the study protocol (Fig. 1 and Table 1). Trial progression or protocol modification will be updated in the registered database (Pan African Clinical Trial Registry, PACTR) and reported to the LUTH's ethical committee that will provide the oversight functions of data and safety monitoring in the course of the study.

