### Confirmatory outcome variables

2.6

Primary endpoints – Preterm birth (delivery before 37 completed weeks of pregnancy) and low birth weight in term neonates (baby's birth weight less than 2.5 kg).

Secondary endpoints – HIV disease progression (change in CD4 + cells count, viral load and stage of the disease); mid-trimester miscarriage, change in haemoglobin levels; adverse events (AE) such as hepatotoxicity, gastrointestinal disturbances, dermatologic effects (nail and hair loss and dermatitis), and neurotoxicity; and perinatal mortality (number of stillbirths and neonatal deaths in the first week of life).

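### Changes in CD4, viral load and haemoglobin are to be compared without covariates or adjusted only by binary logistic regression; a baseline-adjusted linear model would be more precise at no data cost

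*Protocol article*

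**What the plan says.** All references are to the protocol article.

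- **Endpoints (2.6).** The secondary endpoints include "HIV disease progression (change in CD4 + cells count, viral load and stage of the disease") and "change in haemoglobin levels". CD4, viral load and haemoglobin are continuous; disease stage is categorical and lies outside this point. Section 2.7.1 treats HIV disease progression as the major secondary endpoint and sets the total of 180 by it.
- **Unadjusted tests (2.8).** "The associations between any 2 groups of continuous variables will be tested using the independent sample or paired" *t* test when data are normal, or the "Mann-Whitney *U* test (skewed data"). One general sentence covers all continuous variables and assigns no test to any endpoint.
- **Adjusted analysis (2.8).** "A series of multivariable analyses using binary logistic regression model will also be carried out to identify and control for several possible confounders". The scope is the "confounders of the primary and secondary outcome variables". No covariate is named, and no linear or baseline-adjusted model appears.
- **Data collected (2.5.1).** Enrolment data include CD4, viral load, haemoglobin and "type and duration of ART use (in months"). The latest CD4, viral load and haemoglobin are taken again at delivery, along with compliance and total duration of supplement intake.
- **ART (2.4).** "All women will also be commenced on ART at some point during their follow-up". Since ART history is also recorded at entry, the article allows for women already treated and women who start later. It does not give the proportions.

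**The concern.** Three features of section 2.8 fit these endpoints poorly.

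1. The only route to adjustment is a binary model. Applied to a continuous change it needs a cut-point, which discards information, and none is stated.
2. A paired *t* test compares a woman with herself. Where ART begins during follow-up, a within-arm change can reflect ART in either arm and says nothing about the difference between arms.
3. Covariates are to be identified in the course of modelling. In a randomised comparison, adjustment covariates should be chosen before outcome data are seen. The wording does not confine the choice to baseline variables, and section 2.5.1 records items that arise after randomisation. Supplements run until delivery (2.3), so duration of intake depends partly on gestational age at delivery, which defines the primary endpoint of preterm birth.

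At stake is precision on the endpoint that sets the sample size, and protection of the adjusted results from selective or post-randomisation covariate choice.

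**Working it through.** **The plan's own figure.** Section 2.7.1 gives an effect size of 0.3, Z values 1.96 and 1.64, and 20% drop-out. Then (1.96 + 1.64)² / 0.3² = 12.96 / 0.09 = 144, and 144 / 0.80 = 180. This matches, but the formula is the one-sample or paired one, and 1.64 is the value for 95% power, not the 80% printed. A two-sample calculation at 80% gives 175 per arm, 350 in total, 438 with drop-out. That is a separate matter. It is relevant here because precision is scarce and because section 2.8 should leave no doubt that the comparison is between arms.

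**Inputs.** 90 randomised per arm, so 90 × 0.80 = 72 evaluable; two-sided 5%; effect 0.3 (SD scale not stated). *Assumed:* baseline to follow-up correlation r from 0.3 to 0.7, and equal variances at the two times.

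**Variance ratio.** With unit variances, a change score has variance 2(1 − r) and analysis of covariance has residual variance 1 − r². The ratio is (1 − r²) / [2(1 − r)] = (1 + r)/2.

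| r | Ratio | Reduction | Equivalent increase in women (1/ratio − 1) |
|---|---|---|---|
| 0.3 | 0.65 | 35% | 54% |
| 0.5 | 0.75 | 25% | 33% |
| 0.7 | 0.85 | 15% | 18% |

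The direction does not depend on equal variances. With baseline SD s0 and follow-up SD s1, the change-score variance minus the covariance-adjusted variance is (s0² + s1² − 2r·s0·s1) − s1²(1 − r²) = (s0 − r·s1)², which is never negative.

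**Power at 72 per arm.** Power = Φ(0.3·√(72/2)/SD − 1.96) = Φ(1.8/SD − 1.96).

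| 0.3 is expressed in | Analysis | r = 0.3 | r = 0.5 | r = 0.7 |
|---|---|---|---|---|
| change-score SDs | change-score *t* test | 43.6% | 43.6% | 43.6% |
| change-score SDs | covariance-adjusted | 60.7% | 54.7% | 49.7% |
| follow-up SDs | change-score *t* test | 33.0% | 43.6% | 64.2% |
| follow-up SDs | covariance-adjusted | 47.1% | 54.7% | 71.2% |

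Adjustment helps in every column but does not reach 80% in any. For 80% with adjustment, the total including drop-out runs from 285 (r = 0.3) to 373 (r = 0.7) on the change-score scale, and from 398 to 223 on the follow-up scale.

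**What a cut-point would cost, if one were used.** A median split of an outcome with a 0.3 SD difference compares Φ(0.15) with Φ(−0.15). Power at 72 per arm is about 29.7%, against 43.6% for the undivided outcome.

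**Chance imbalance in ART.** Section 2.3 names no stratification by ART. If half the women are on ART at entry (assumed), the SD of the arm difference in that proportion with 90 per arm is √(2 × 0.25/90) = 0.0745. The chance of a difference of 10 points or more is 2[1 − Φ(0.10/0.0745)], about 18%.

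**What adjusting for ART adds.** A simulation used 72 per arm, a true effect of 0.3, half on ART and an ART effect of 0.5 SD (all but the first two assumed). Mean estimates were between 0.292 and 0.304 for every method, adjusted or not. At r = 0.5, adding ART to the baseline-adjusted model reduced the standard error from 0.150 to 0.145.

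**The case against.** The strongest reply is that the planned between-arm test is sound and that the rest is detail an article may leave to a fuller document. Much of this stands, and it rules out several stronger readings.

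- *The tests ignore baseline.* They do not. The endpoints are changes, so a *t* test on change uses the baseline by subtraction. The point is that subtraction is less efficient than regression on baseline.
- *Selenium will be judged by paired tests.* A reader might infer this from the general sentence, but no test is assigned to any endpoint. Paired tests may be meant only for before-and-after description. The text should say so.
- *Outcomes will be split at the median, or adjusted for supplement duration.* Neither is announced. The cost of a split is what the binary model would entail if used on a change, and the exclusion of post-randomisation covariates is a safeguard.
- *ART imbalance biases the trial or can swamp the effect.* Randomisation prevents systematic imbalance, and chance imbalance is already in the standard error. With half on ART, an ART difference of δ contributes 0.25δ² to the variance, so δ cannot exceed 2 SDs. A 10-point imbalance then shifts the contrast by at most 0.20 SD, and by 0.05 SD if δ is 0.5 SD.
- *Viral load may be skewed, with values below the assay limit.* This is fair. Mann-Whitney covers the skew, and a linear model on the log scale needs a rule for undetectable values.

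The argument from brevity does not dispose of the point. Section 2.8 makes a definite choice: one type of adjusted model, for primary and secondary outcomes, with covariates found during analysis. That model does not fit three of the continuous endpoints.

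**Conclusion.** The point holds as a moderate improvement to the stated analysis, not as an error that invalidates it. The planned between-arm test on change is valid and unbiased. Replacing it with a baseline-adjusted linear model lowers the variance by 15% to 35%, for r between 0.7 and 0.3 and equal variances at the two times. The article supplies neither input, so the size is indicative while the direction is not in doubt. ART adjustment brings a smaller further gain and corrects only chance imbalance in ART measured at entry; ART begun after randomisation is untouched. Binary logistic regression is the wrong tool for continuous changes, and the covariate wording should be closed off because it also covers the primary endpoints. None of this makes 180 women sufficient for an effect of 0.3 between arms.

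**What to change.** Amend section 2.8 as follows.

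1. Compare arms on delivery-time CD4, log10 viral load and haemoglobin by linear regression on arm, the baseline value of the same variable and ART status at enrolment. For viral load, state a rule for values below the assay limit or use a rank-based equivalent.
2. Limit paired tests to within-arm description.
3. Keep logistic regression for binary endpoints. List its covariates in advance and restrict them to variables measured at or before randomisation. That excludes ART started later, compliance and duration of supplement intake.

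The cost is wording only. Every variable needed is already collected under section 2.5.1, and the named software can fit the models. The sample-size calculation in section 2.7.1 needs its own correction.

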#### Sample size

2.7.1

Using the data from our previous study,^[11]^ we propose to enrol 148 participants in the study to investigate the effect of selenium supplementation on the primary endpoints. The study is powered for a 2-sided test with a Type I error rate of 5% and 95% power, that is, Z_α_ = 1.96 and Z_β_ = 1.64, adjusted for a 20% drop-out rate. We also propose to enrol 180 participants to detect an effect size of 0.3 of selenium supplementation on the major secondary endpoint (reduction in HIV disease progression). This is powered for a 2-sided test with a Type I error rate of 5% and 80% power, that is, Z_α_ = 1.96 and Z_β_ = 1.64, adjusted for a 20% drop-out rate. Therefore, a total sample size of 180 is used in this study with 90 HIV-infected women randomised into each of the trial arms to assess the effects of selenium supplementation on the primary and secondary outcome variables.

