## Discussion

3

Selenium is a non-metallic chemical element of great important to human health. Biochemical selenium deficiency has been associated with increased mortality among those infected with HIV and with accelerated HIV disease progression. This study aims to assess the effects of giving routine antenatal selenium supplementation to HIV-infected pregnant women on their pregnancy outcome and HIV-disease progression. If it is found to be significantly effective and safe, this trial will provide a basis for prescribing this antioxidant to HIV-seropositive women in pregnancy.

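### Two primary endpoints share one unsplit 5% error rate and a flat P < .05 with no success rule; if either one suffices, the two-sided family-wise error is about 9.75%

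*Protocol article*

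**What the plan says.** Four places in the protocol article bear on this.

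- **Section 2.6** has the heading "Confirmatory outcome variables" and lists as primary "Preterm birth (delivery before 37 completed weeks of pregnancy) and low birth weight in term neonates". It gives the two no order of priority. The secondary list, which opens with HIV disease progression, stands under the same heading.
- **Section 2.7.1 (Sample size)** makes one calculation for the primary endpoints together: "The study is powered for a 2-sided test with a Type I error rate of 5% and 95% power". It does not divide the 5%. It arrives at 148 enrolled for the primaries and adopts 180 because of the major secondary endpoint.
- **Section 2.8 (Statistical analyses)** names chi-square or Fisher's exact test for categorical outcomes and ends with one rule: "Statistical significance will be defined as *P* < .05".
- **Section 3 (Discussion)** says what success would lead to: "If it is found to be significantly effective and safe, this trial will provide a basis for prescribing this antioxidant". It does not say on which endpoint, or on how many, the supplement must be effective.

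**The concern.** A threshold and an error rate are both stated, and they agree only under a success rule that the article does not give. A 5% error for the primary endpoints as a set holds if both must reach P < .05, or if the 5% is shared or spent in sequence. It does not hold if each is tested at .05 and either may be claimed.

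As written, a reader who follows section 2.8 may declare success on whichever primary crosses the line. The choice of which primary counts could then be made after the results are known, and the stated 5% would not be the error rate behind a recommendation to prescribe.

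**Working it through.** **Inputs.** Two primary endpoints (section 2.6); two-sided alpha 0.05 per test (sections 2.7.1 and 2.8); 95% power with 148 enrolled, 180 adopted, 20% drop-out in both (section 2.7.1). The article gives no event rates or effect size for the primaries, so 148 cannot be reproduced. The stated 95% power is taken as given below.

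**1. The stated figure.** For one two-sided test at P < .05 the error is 5%, that is, 2.5% in the direction of benefit. The stated 5% is therefore right for each primary on its own.

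**2. Either primary suffices.** Under independence:
- Both directions: 1 − 0.95² = 0.0975. Under any dependence it cannot exceed 0.05 + 0.05 = 0.10.
- Benefit only: 1 − 0.975² = 0.0494, against 0.025 for one test.

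With correlated test statistics (bivariate normal), the two-sided figure falls slowly:

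| Correlation | At least one P < .05 |
|---|---|
| 0 | 9.75% |
| 0.3 | 9.5% |
| 0.5 | 9.1% |
| 0.7 | 8.3% |

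**3. Both primaries required.** The chance of a false claim is at most 5% whichever null is true. If both nulls are true and the tests independent, it is 0.05² = 0.25%. There is no inflation.

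**4. Effect of the test used.** Simulation under the null tested preterm birth in all women and low birth weight in term births only. The rates are assumptions: preterm 10–30%, term low birth weight 5–20%.
- Chi-square without continuity correction, 72 or 90 per arm: family-wise error 9.5–9.9%.
- Fisher's exact test throughout, same sizes: about 4.5–7.0%, because that test is conservative with small counts.

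**5. Power if the 5% is shared.** With 95% power at two-sided .05, the standardised effect at 148 enrolled is 1.960 + 1.645 = 3.605. The two-sided critical value at .025 is 2.241.
- At 148: Φ(3.605 − 2.241) = Φ(1.363) = 91.4%.
- At 180: 3.605 × √(180/148) = 3.975; Φ(3.975 − 2.241) = Φ(1.734) = 95.9%.
- Enrolment that restores 95% at .025: 148 × [(2.241 + 1.645)/3.605]² = 148 × 1.162 = 172, which is below 180.

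Holm tests the smaller P value at .025 and, if that succeeds, the other at .05. These powers are therefore lower limits for each endpoint under Holm.

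**The case against.** **The rule may be a both-required rule, or may sit in a document not shown.** This stands in part. The Discussion requires neither one nor both, so the inflation is conditional. A full protocol or analysis plan could add an adjustment, and the absence of that detail from an article would be no finding. But the article does fix a flat threshold and an unsplit error rate, and any such adjustment would have to change the threshold it states.

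**The figure may not be reached in practice.** This stands. Section 2.8 allows Fisher's exact test, which brings the error close to 5% when counts are sparse. It also names chi-square, so the plan cannot rely on that protection.

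A reader might draw stronger conclusions, which the document does not support:

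- *That a false claim of efficacy has a chance near 10%.* The 9.75% counts significant results in both directions, including apparent harm. For benefit alone it is about 4.9% against 2.5%. The doubling is real, but the level is half.
- *That the heading of section 2.6 makes every secondary outcome a confirmatory test, with a 40% chance of some false positive* (1 − 0.95¹⁰ for ten items). That count includes four kinds of adverse event, where a false signal confirms no efficacy. The six others would give 1 − 0.95⁶ = 26% under independence, but CD4 count, viral load and stage all measure disease progression, so independence is not realistic. Sections 2.6 and 2.7.1 also separate primary from secondary. The heading is a wording fault.
- *That the two primaries are independent because no woman can have both.* Mutually exclusive events are not independent. The near-independence of the tests comes from assessing low birth weight among term births only.
- *That preterm birth should come first.* Nothing in the article ranks the two.

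**Conclusion.** The point holds as a conditional one. Sections 2.6, 2.7.1 and 2.8 together leave the success rule open, while fixing a threshold that keeps the stated 5% only if both primaries are required. If either suffices, the two-sided family-wise error is about 9.75% with independent tests of full nominal size, 9.1% at correlation 0.5, and roughly 4.5–7.0% if Fisher's exact test is used throughout under the assumed rates. The chance of a false claim of benefit is about 4.9% instead of 2.5%. If both are required, the 5% is kept.

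The arithmetic for the either-one rule is not in doubt. What the article leaves unsettled is whether that rule applies, and that is what needs to be stated.

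**What to change.** In section 2.8, replace the flat threshold for the two primaries with one of these, chosen by the sponsor before unblinding:

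- Holm or Hochberg across the two at an overall two-sided 5%. Holm needs no assumption about how the tests are correlated.
- A statement that both must reach two-sided P < .05 for the trial to succeed.
- A fixed order, each at two-sided 5%, with the second tested only if the first succeeds. The order is the sponsor's choice.

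In section 2.6, limit the word 'Confirmatory' to the primaries, and in section 2.8 treat secondary P values as supportive.

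**Cost.** One or two sentences. Under Holm, the protocol's own figures give at least about 91% power per endpoint with 148 enrolled and about 96% with the adopted 180, against the planned 95%, so they imply no shortfall. A both-required rule gives at least 1 − 0.05 − 0.05 = 90% with 148, if each primary has 95%. A fixed order costs the first endpoint nothing. All of this rests on the stated 95% power at 148 being right for each primary, which the article gives no event rates to check. Section 3.1 says recruitment had not begun at submission, and section 2.3 keeps investigators blinded until after the final analysis, so the rule can be set without sight of results by arm.

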### Discontinuation of study intervention (code-breaking) and Reporting

2.9

The PI may choose to discontinue a participant from the study for reasons such significant failure to compliance with study intervention, serious adverse event (SAE) such as significant renal or hepatic impairment or suspected unexpected serious adverse reaction (SUSAR), that is, medical condition or situation in which continued participation in the study would not be in the best interest of the participant (code-breaking). The event causing study intervention discontinuation will then be documented in a dedicated Case Report Form (CRF) that would capture the date and the specific underlying reason for discontinuation of study intervention.

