### Study population/ participant enrolment

2.2

Eligible participants are confirmed HIV-seropositive pregnant women aged 15 to 49 years who have a singleton gestation at 14 to 27 weeks’ gestation. The exclusion criteria at enrolment are multiple gestations, significant renal and hepatic impairment, an expected delivery date beyond March 2019, receipt of a long course of mineral supplement containing selenium during the 6 months prior to enrolment, refusal of consent at enrolment or withdrawal of consent during the study.

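### Section 2.9 does not separate stopping tablets from leaving the study; read as study exit, removal for non-compliance conflicts with intention-to-treat and can lose primary outcomes selectively

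*Protocol article*

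**What the plan says.** Five places in the protocol article bear on this.

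- **Section 2.9, the rule:** "The PI may choose to discontinue a participant from the study for reasons such significant failure to compliance with study intervention". The same sentence adds serious adverse events and suspected unexpected serious reactions, and describes these as situations in which remaining in the study would not serve the woman's interest.
- **Section 2.9, the record:** "The event causing study intervention discontinuation will then be documented in a dedicated Case Report Form (CRF"), with the date and the reason. This sentence and the section heading refer to stopping the intervention, not to leaving the study.
- **Section 2.5.1:** data collection "continues until the termination of the trial or until the participant withdraws from the trial at any time for any reason". The same section sets a compliance cut-off: "good compliance level is defined as usage of at least 10 of the 16, 2-weekly prescribed tablets".
- **Section 2.2:** the exclusion criteria at enrolment end with "refusal of consent at enrolment or withdrawal of consent during the study".
- **Section 2.8:** "The intention-to-treat principle will be used in the final analyses".

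The primary endpoints in section 2.6 are "Preterm birth (delivery before 37 completed weeks of pregnancy) and low birth weight in term neonates".

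**The concern.** Non-compliance after randomisation is what an intention-to-treat analysis is meant to absorb. A rule that lets the investigator take a woman out of the study because she does not take her tablets works against that principle if it also ends collection of her outcomes.

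The timing makes this matter. Both primary endpoints become known only at delivery, so a woman who leaves earlier has neither. The second endpoint is confined to term neonates, so without a gestational age at delivery she cannot even be placed in or out of its denominator. An analysis plan written later cannot recover outcomes that were never collected.

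The loss need not be random. Poor compliance and serious adverse events can reflect tolerability, illness or social circumstances, which may also be related to preterm birth. If they differ by arm, the comparison of the remaining women is biased. The article gives a cut-off for good compliance but none for the significant failure that allows removal, so the decision rests on judgement and can arise at any of the 2-weekly pill counts (section 2.3).

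**Working it through.** **1. The passages side by side**

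| Question | What the article says |
|---|---|
| What is discontinued? | Section 2.9, rule: participation in the study. Section 2.9, heading and form: the intervention. |
| When does data collection end? | Section 2.5.1: at trial termination, or when the participant withdraws. Removal by the investigator is not mentioned. |
| Are women off tablets followed to delivery? | Not stated in any text shown. |
| Who is analysed? | Section 2.8: intention-to-treat. |
| How is consent withdrawal treated? | Section 2.2: as an exclusion at enrolment, although it can only happen afterwards. |

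Two readings are open. If section 2.9 means stopping tablets only, there is no conflict with section 2.8, but the words of the rule are wrong. If it means leaving the study, the conflict is real.

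**2. The plan's own allowance for loss**

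Section 2.7.1 states that "a total sample size of 180 is used in this study with 90 HIV-infected women randomised into each of the trial arms", including 20% drop-out. With the printed Z values and effect size 0.3:

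(1.96 + 1.64)² / 0.3² = 12.96 / 0.09 = 144, and 144 / (1 − 0.20) = 180.

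So 180 is reproduced, and the allowance is 180 × 0.20 = 36 women, or 18 per arm, leaving 72. (The formula and the stated power behind 180 raise separate questions that do not affect this point.) The allowance covers drop-out from all causes; the plan does not say how much would come from removal by the investigator.

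If 18 women per arm had no delivery outcome, the best-case to worst-case bounds on the difference in preterm risk would span 18/90 + 18/90 = 40 percentage points.

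**3. Illustration of bias with no true effect**

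The article gives no preterm risk and no removal rate, so all inputs here are assumptions. Let p be the true preterm risk in both arms, f the fraction removed in an arm, and r the risk in removed women relative to p. The risk among those kept is

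(p − f·r·p) / (1 − f).

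| p | r | f, selenium v placebo | Kept, selenium | Kept, placebo | Spurious difference |
|---|---|---|---|---|---|
| 20% | 2 | 20% v 20% | 15.0% | 15.0% | 0 |
| 15% | 1.5 | 10% v 5% | 14.2% | 14.6% | −0.4 points |
| 20% | 2 | 20% v 10% | 15.0% | 17.8% | −2.8 points |
| 30% | 3 | 20% v 5% | 15.0% | 26.8% | −11.8 points |

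Third row in full: (0.20 − 0.20 × 0.40)/0.80 = 0.150 and (0.20 − 0.10 × 0.40)/0.90 = 0.178.

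The second and last rows are the extremes for unequal removal over p of 15, 20 and 30%, r of 1.5, 2 and 3, and removal of 10 v 5, 15 v 5, 20 v 10 and 20 v 5%. The sign reverses if more women are removed from placebo.

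**The case against.** The strongest reply is that section 2.9 is about stopping treatment. Its heading and its form sentence say so, section 2.8 commits to intention-to-treat, and nothing says that a discontinued woman leaves the analysis set. Removal is discretionary, and the adverse-event trigger is a serious event, not any side effect. Investigators are blinded, which limits removal that favours one arm. The article is condensed: section 2.10 mentions training in exit criteria and follow-up procedures, and the flow chart and schedule are not visible, so follow-up after discontinuation may be set out elsewhere.

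Much of this stands, and it rules out several stronger readings that a reader might draw:

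- **That data collection stops when the investigator removes a woman.** Section 2.5.1 ties the end of data collection to withdrawal by the participant. Extending it to removal is an inference.
- **That the analysed women would all be compliant and event-free.** Section 2.5.1 records compliance level together with the delivery data, and section 2.6 makes gastrointestinal and skin effects secondary endpoints. Women with poorer compliance or side effects are evidently expected to remain.
- **That delivery outcomes can simply be looked up in case notes.** Section 2.5.1 names case notes as the source for CD4 count, viral load, disease stage and haemoglobin. Gestational age at delivery and birth weight are recorded in the questionnaire, with no such source stated.
- **That consent withdrawal itself breaches intention-to-treat.** Ending data collection when consent is withdrawn is legitimate. Only its place among the enrolment exclusions is wrong.
- **That full follow-up would restore 90 women per arm.** The 20% covers all drop-out, so not every lost woman would be recovered.

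The reply does not remove the wording of the rule. It names leaving the study, gives non-compliance as a reason, and refers to continued participation in the study. This is a stated rule at odds with a stated principle, not a detail left to another document.

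**Conclusion.** The point holds as a conflict of wording with a real route to bias. Section 2.9 uses one procedure for two different acts, and under one of its two natural readings it defeats section 2.8 for both primary endpoints.

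The size cannot be determined from the article. The bias is zero when removal is equal and equally related to outcome in both arms, and about 0.4 to 12 percentage points under the assumed inequalities shown. The upper end needs 20% v 5% removal and a 90% preterm risk among removed women, so it is an outer limit and not an expectation. The drop-out allowance replaces numbers but does not remove bias.

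The slip in section 2.2 is minor. Overall this should be fixed, but because the study-exit reading is not the only one, it is not shown that the trial as written would lose these outcomes.

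**What to change.** Reconcile sections 2.2, 2.5.1, 2.8 and 2.9 so that they state:

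- Stopping tablets, for whatever reason, is not withdrawal from the study.
- Non-compliance alone does not end study participation or outcome collection.
- Gestational age at delivery, birth weight and the secondary and safety outcomes are sought to delivery (perinatal deaths to the end of the first week of life, as section 2.6 defines them), unless the woman withdraws consent to data collection.
- All randomised women are analysed in their assigned arm. Withdrawal of consent is treated as post-randomisation missing data and removed from the exclusion criteria.
- The discontinuation form records separately whether tablets were stopped and whether consent to further data collection was withdrawn.

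The cost is wording in the protocol and form, and a small amount of extra follow-up at delivery for women off tablets. Section 3.1 says recruitment had not begun at submission, when such a change is cheapest. When tablets should be stopped is a clinical decision and is not addressed here.
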